## **8.5 Description of Statistical Analyses**

### **8.5.1 General Considerations**

All tabulations will be done by treatment group (current PZQ crushed and dispersed in water, Rac-PZQ ODT with water, L-PZQ ODT with water, Rac-PZQ ODT no water, L-PZQ ODT no water).

#### **8.5.1.1 Subject Demographics**

Baseline demographic and medical and medical history variables will be summarized for all subjects, overall and for each of the treatment group. For categorical variables, frequencies and percentages will be presented. Continuous variables will be summarized using descriptive statistics (mean, median, standard deviation, quartiles (25th, 75th), minimum, maximum).

#### **8.5.1.2 Subject Accountability**

The number of subjects who enrolled into the study, the number planned to be enrolled in each sequence, and the number and percentage of these subjects who were enrolled and completed each assessment will be presented. Frequency and percentage of subjects, who withdrew from the study, and reason for withdrawing, will be summarized overall and by treatment and treatment-sequence.

#### **8.5.1.3 Vital signs and physical evaluation**

Vital signs (Respiratory rates, heart rates and Temperature) and physical evaluation will be summarized for all subjects, overall and for each of the treatment group at each time point. For categorical variables, frequencies and percentages will be presented. Continuous variables using

value and change from baseline value will be summarized using descriptive statistics (mean, median, standard deviation, quartiles (25th, 75th), minimum, maximum).

### **8.5.2 Analysis of Primary Endpoints**

VAS at time t0 will be summarized using descriptive statistics (mean, median, standard deviation, quartiles (25th, 75th), minimum, maximum) by treatment group.

The first alternative hypothesis (HA1) that the two formulations Rac-PZQ (no water) and L-PZQ (no water) differ in taste, as opposed to the H01 (the two formulations are similar) will be tested using a repeated measure ANOVA with factors time, sequence, treatment and stratification factor of sex and age (in categories). A contrast statement at Time 0 to compare the two formulation based on the likelihood ratio test will be conducted at two-sided 5% significance level.

The second alternative hypothesis (HA2) that at least one of the two new formulations (with water) differs in taste from the “current PZQ formulation” will be tested using a repeated measure ANOVA with factors time, sequence and treatment and stratification factor of sex and age (in categories) will be used.

Contrast statement at Time 0 to compare

- Rac-PZQ ODT (with water) vs current PZQ (crushed with water), and
- L-PZQ ODT (with water) vs current PZQ (crushed with water)

It will be done using the likelihood ratio test. These tests will be performed at an alpha level of 2.5% to account for the multiplicity of testing.

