## 5.2 Discussion of Trial Design

The trial will enrol infected and non-infected children, and diagnosis of schistosomiasis will not be made and is not part of the inclusion criteria. According to the EU guidance “Ethical considerations for clinical trials on medicinal products conducted with the pediatric population” it is acceptable to conduct swill and spit taste study in healthy children. However, following the Advisory Board Expert meeting held in August 2013 in Geneva, inclusion of infected children was deemed appropriate and it was recommended to provide a prophylactic post-medication therapeutic dose treatment of Praziquantel to all children who have participated to the trial after the study ends (according to WHO SOPs). It was also recommended at this Expert meeting to avoid exposing children to unnecessary taste fatigue (due to the unpleasant taste of PZQ and the number of treatment arms), as recommended in the CHMP guidance (CHMP, 2005) and to limit as much as possible the number of tablets of PZQ per treatment arm. Hence, a single tablet (150 mg L-PZQ ODT, 150 mg rac-PZQ ODT or ¼ of the Cesol 600 mg tablet) is administered in the trial. To avoid taste fatigue the 5 taste assessments have been spread over two days.

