#### **8.1 Sample Size**

A total sample size of 48 subjects is considered adequate to fulfil the objective of the study.

Considering the design Day 1 (2 treatments), Day 2 (3 treatments) with the fact that the same subjects will be treated in both days, the stratification constraint by sex (female/male 1:1 ratio) and age (<9 yrs and ≥9yrs 1:1 ratio), the sample size should be a multiple of 24.

DAY 1: A total of 48 subjects (24 subjects per sequence) will provide at least 89.2% power to detect a 10 pts mean difference in VAS overall palatability between Rac-PZQ ODT (no water) and L-PZQ ODT (no water), assuming a within-subject standard deviation of 15 pts (square root of within subject MSE), and a two-sided type 1 error of 5.0%.

DAY 2: A total of 48 subjects (8 subjects per sequence, 6 sequences due to 3 treatments-3 periods) will provided at least 92.4% power to detect a 20 pts mean difference in VAS overall palatability between one of the new formulations Rac-PZQ (with water) or L-PZQ (with water) and the current PZQ formulation crushed in water, assuming a within-subject standard deviation

of 15 pts (square root of within subject MSE), and a two-sided type 1 error of 2.5%, to adjust for the multiplicity.

Software East 6.2 was used for the sample size calculation.

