## 8.2 Randomization

Subjects will be randomized in blocks by sex (male/female 1:1 ratio) and age (<9 yrs and ≥9yrs 1:1 ratio) in one of the following treatment-sequence

Day 1: 2 treatments (no water) - 2 period cross-over

F1: Rac-PZQ ODT - L-PZQ ODT

G1: L-PZQ ODT - Rac-PZQ ODT

Day 2: 3 treatments (dispersed/crushed in water) - 3 period cross-over

H2: L-PZQ ODT - Rac-PZQ ODT- PZQ 150 mg

J2: L-PZQ ODT– PZQ 150 mg - Rac-PZQ ODT

K2: Rac-PZQ ODT– PZQ 150 mg - L-PZQ ODT

L2: Rac-PZQ ODT - L-PZQ ODT – PZQ 150 mg

M2: PZQ 150 mg - L-PZQ ODT- Rac-PZQ ODT

N2: PZQ 150 mg - Rac-PZQ ODT- L-PZQ ODT

The randomization list will be prepared by Swiss TPH.

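### The primary cross-over models contain no period factor, so any shift between tastings inflates the within-child error; this can take Day 1 power below the stated 89.2%, but does not undercut the stated Day 2 power

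*Protocol*

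**What the plan says.** Protocol section 8.2 randomizes children to two orders on Day 1 and six on Day 2 ("Day 2: 3 treatments (dispersed/crushed in water) - 3 period cross-over"). Section 7.1.2 says the assignment is meant to balance the order of tasting across gender and age groups.

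The analysis model appears in three places:

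- Section 8.5.2: time, sequence, treatment, sex and age for Day 1, and the same list for Day 2 ("using a repeated measure ANOVA with factors time, sequence and treatment and stratification factor of sex and age (in categories) will be used"). The Day 1 contrast is taken at Time 0, "based on the likelihood ratio test will be conducted at two-sided 5% significance level".
- Synopsis, primary endpoints: time, sequence, treatment, age and sex.
- Section 4: sequence, treatment, age and sex, without time.

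None of the three includes period. Section 8.3.1 defines Time 0 as the score given right after spitting out, and section 8.3.2 makes the 2-5 min score secondary. The factor *time* therefore separates two scores of the same tasting, not first from later tastings.

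On fatigue, section 5.2 says: "To avoid taste fatigue the 5 taste assessments have been spread over two days". On power, section 8.1 states for Day 1 "A total of 48 subjects (24 subjects per sequence) will provide at least 89.2% power to detect a 10 pts mean difference", and for Day 2 "A total of 48 subjects (8 subjects per sequence, 6 sequences due to 3 treatments-3 periods" with "at least 92.4% power to detect a 20 pts mean difference in VAS overall palatability". Both figures assume a within-subject SD of 15 points, taken as the square root of the within-subject MSE.

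**The concern.** Balancing the order of tasting lets a period effect be separated from the treatment effect, but the analysis gains precision from this only if period is in the model. Sequence, sex and age are constant within a child, so they cannot absorb a change in scoring between a child's first and last tasting. Treatment cannot absorb it either, because each formulation occurs equally often in each period. The shift is left in the within-child residual, which is the quantity on which the power statement rests.

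The protocol itself gives reason to allow for such a shift: it names taste fatigue as a risk, and two or three tastings of an unpleasant drug still fall on one day, about an hour apart. At stake are power for the Day 1 comparison of the two ODTs, correct calibration of both tests, and protection from bias if the analysed sequences are unequal.

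**Working it through.** **Inputs.** From section 8.1: N = 48; within-subject SD 15; Day 1 difference 10 points at two-sided 5%, 24 children per sequence; Day 2 difference 20 points at two-sided 2.5%, 8 children per sequence. Assumed, because the protocol gives no figure: a period shift of 0 to 20 mm (Day 1: second against first tasting; Day 2: a linear drop per period). One Time 0 score per tasting is analysed, with child as the within-subject term. This simplifies the stated model, which also carries the 2-5 min score.

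**The plan's own figures.** SE of a treatment contrast = 15 × √(2/48) = 3.062.

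- Day 1: 10/3.062 = 3.266. The noncentral t with 46 df gives 89.2%, as stated.
- Day 2: 20/3.062 = 6.532. With 92 df and 2.5% this gives more than 99.99%, not 92.4%. The protocol's figure is worded as a lower bound, so it is not strictly false, but it does not follow from the cross-over inputs.

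**Day 1 without period.** A child's treatment difference has variance 2 × 15² = 450. With a shift π, the two sequences have mean differences δ − π and δ + π. With 24 children in each, π cancels from the average, so the estimate is unbiased and its true SE stays at 3.062. The residual variance, estimated on 47 df, now has expectation 450 + π² × 48/47. The estimated SE is therefore inflated by r = √[(450 + π² × 48/47)/450], and the effective critical value is 2.012 × r.

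For π = 10: 450 + 102.1 = 552.1, r = 1.108 and the critical value is 2.228. Power is roughly Φ(3.266 − 2.228) = Φ(1.038) = 85%. Simulation (40,000 runs) agrees:

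| Assumed shift (mm) | r | Power, no period | Power, with period | Size of 5% test, no period |
|---|---|---|---|---|
| 0 | 1.000 | 89% | 89% | 4.9% |
| 5 | 1.028 | 88% | 89% | 4.5% |
| 10 | 1.108 | 85% | 89% | 3.0% |
| 15 | 1.229 | 78% | 89% | 1.6% |
| 20 | 1.381 | 69% | 89% | 0.8% |

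The shift must not be added to the variance of the estimate itself. That would treat it as random noise and overstate the loss.

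**Day 2 without period.** A drop of s per period gives each child centred period values of s, 0 and −s, with sum of squares 2s². The expected residual mean square on 94 df is 225 + 48 × 2s²/94. For s = 10 this is 225 + 102.1 = 327.1, so r = √(327.1/225) = 1.206 and the effective critical value is 2.278 × 1.206 = 2.747. Simulation (20,000 runs):

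| Assumed drop per period (mm) | Power at 20 points, no period | Size of 2.5% test, no period |
|---|---|---|
| 0 | >99.9% | 2.4% |
| 5 | >99.9% | 1.8% |
| 10 | >99.9% | 0.7% |
| 15 | >99.9% | 0.1% |
| 20 | 99.6% | 0.01% |

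With period in the model the simulated size lies between 2.3% and 2.5% throughout.

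**Unequal sequences.** The shift then no longer cancels, and the bias is π × (n₂ − n₁)/N. A deliberately extreme 20/28 split with a 10 mm shift gives 10 × 8/48 = 1.7 mm.

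**Likelihood ratio test.** If it is referred to chi-square with 1 df, the statistic n·log(1 + t²/df) has, with period in the model, true size 5.6% for nominal 5% (n = 48, df 46) and 2.9% for nominal 2.5% (n = 96, df 92).

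**The case against.** The strongest reply is that the design already limits the problem. The tastings are split over two days, the washout is about an hour, and the palate is cleansed before and after each tasting. A reader might infer from section 5.2 that the protocol expects fatigue. It does not: it names a risk that the design is meant to reduce, and it neither predicts nor sizes a period effect. At 5 mm the Day 1 loss is about one point. This stands, and every loss shown here is conditional on an assumed shift.

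A reader might also infer that the stated Day 2 power is cut. It is not, at the planned 20 points. Power drops noticeably only for a smaller Day 2 difference such as 10 points (about 84% with no drift, 70% at 10 mm per period), which is not the planned effect.

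On bias, section 7.1.3 gives a replacement child the same randomization code, which restores balance among completers. The Full Analysis Set in section 8.4.1, however, keeps every assigned child, so a dropout's Day 1 scores can still tip the sequences there.

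Finally, it is tempting to count the likelihood ratio test as a second fault that makes the tests liberal. The excess is at most 0.6 percentage points. It presumes a chi-square reference that the protocol does not name, and the two effects do not add up: with a 10 mm shift left out, the likelihood ratio test has size about 3.3% on Day 1 and 0.8% on Day 2.

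The argument that period can be left to the SAP does not stand, because section 8.5.2 already fixes the factors of the primary test.

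**Conclusion.** The point holds as an omission from a stated model. The practical cost is on Day 1, where the stated 89.2% becomes about 85% at an assumed 10 mm shift and about 69% at 20 mm. On Day 2 the planned power is safe over the assumed range, but the test is well below its nominal level if there is a drift. With balanced sequences there is no bias and no inflation of type I error; bias arises only if the analysed sequences are unequal.

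These sizes rest on the protocol's SD of 15, on assumed shifts, and on one Time 0 score per tasting. The source of the SD is not given; if it came from an analysis without period, part of the loss is already included. The likelihood ratio test is a minor matter.

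**What to change.** Add period as a fixed factor to both primary models in section 8.5.2 (two levels on Day 1, three on Day 2), with child as the within-subject term. Make the model statements in the synopsis, section 4 and section 8.5.2 agree. The cost is wording plus 1 df on Day 1 and 2 df on Day 2; power then no longer depends on the size of the period effect.

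Optionally, replace the likelihood ratio test with a t or F contrast and a stated method for the degrees of freedom (for example REML with Kenward-Roger), which restores the nominal 5% and 2.5%.

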To address the gap of non-treatment of pre-SAC children, a Praziquantel pediatric consortium has been set-up under the umbrella of Top Institute Pharma (TI Pharma, Leiden, Netherlands) with partners from the pharmaceutical industry (Merck Serono, Germany, Astellas Pharma, Japan, SimCyp, UK), the public sector (Farmanguinhos, Brazil) and the academic sector (Swiss Tropical Public and Health Institute –Swiss TPH). In this trial the Ifakara Health Institute (IHI) partners with Swiss TPH to undertake this study in Tanzania. The consortium aspires to develop a new pediatric formulation of PZQ and register its use in the pediatric schistosomiasis indication.

PZQ is a racemic mixture composed of the L-PZQ and D-PZQ enantiomers in a 1:1 ratio. The cidal activity on the worms resides in the L-PZQ enantiomer whereas the D-PZQ enantiomer was suggested to play an important role in the bitterness. Therefore, a new L-PZQ formulation (including taste masking by using mannitol and sweeteners) is expected to give better palatability (less bitterness) than a rac-PZQ formulation. Both L-PZQ and rac-PZQ child friendly oral disintegrating tablet (ODT) formulations for pediatric use are currently under development and the most suitable formulation will be selected in 2015 for further development and registration in children age 3 months to 6 years infected with Schistosomiasis.

This project has been presented and approved by the PZQ Consortium Board in Dec 2013 and the Merck Integrated Clinical Study Committee on the 08 Jun 2014. For further information about the nonclinical and clinical programs and Guidance for the Investigator, please refer to the Investigator's Brochures (IB).

This clinical trial will be conducted in compliance with the clinical trial protocol, ICH GCP, and any additional applicable regulatory requirements.

Based on the available nonclinical and clinical data of PZQ and L-PZQ to date, the conduct of the trial specified in this protocol is considered justifiable.

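### The two Day 2 contrasts are each fixed at 2.5%; Holm's step-down within Day 2 keeps the same 5% bound and never rejects less

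*Protocol*

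**What the plan says.** Section 8.5.2 sets up two hypotheses on the VAS at time 0.

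- **HA1 (Day 1, no water):** one contrast, L-PZQ ODT against Rac-PZQ ODT. The test "will be conducted at two-sided 5% significance level".
- **HA2 (Day 2, with water):** the claim is "that at least one of the two new formulations (with water) differs in taste from the" current formulation. It has two contrasts, Rac-PZQ ODT and L-PZQ ODT, each against the crushed tablet. For these: "These tests will be performed at an alpha level of 2.5% to account for the multiplicity of testing".

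Section 8.1 confirms the sidedness for Day 2: "a two-sided type 1 error of 2.5%, to adjust for the multiplicity". It gives each day its own power statement, both for 48 children and a within-subject SD of 15 points: 89.2% for 10 points on Day 1 and 92.4% for 20 points on Day 2. Section 4 lists the Day 1 and Day 2 comparisons as two objectives. No section states an error rate across both days.

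**The concern.** The protocol fixes the multiplicity rule itself, so this is not a detail left open for the SAP. Dividing 5% by two and testing both contrasts at 2.5% ignores what is known once one of them has been rejected. Holm's procedure uses that information at no cost to the familywise bound.

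What is at stake is the second Day 2 claim. Suppose one ODT is clearly better than the tablet and the other gives a p-value between 2.5% and 5%. The fixed rule cannot declare the second difference; Holm can. With two candidate formulations under comparison, showing that both beat the current tablet is a different result from showing that one does.

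The protocol also does not say that its 5% applies to each day separately. A reader could take the 2.5% as covering the whole primary analysis, which it does not.

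**Working it through.** **Inputs.** From section 8.1: N = 48, within-subject SD 15, Day 1 difference 10 points at two-sided 5%, Day 2 difference 20 points at two-sided 2.5%. From section 8.5.2: two Day 2 contrasts sharing one reference, hence correlation 0.5 under equal variances. Assumed: t-based tests as a stand-in for the likelihood ratio test, with 46 residual df on Day 1 and 92 on Day 2.

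**Step 1: the plan's own figures.** Standard error of a crossover contrast = 15 × √(2/48) = 3.062.

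- Day 1: 10/3.062 = 3.27; noncentral t, 46 df, 5% gives 89.2%. This agrees with section 8.1.
- Day 2: 20/3.062 = 6.53; noncentral t, 92 df, 2.5% gives more than 99.99%. Section 8.1 says at least 92.4%. The closest match found is three parallel groups of 16 (45 df), which gives 92.3%. That mismatch is a separate matter for section 8.1. The crossover value is used below.

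**Step 2: the two rules.** Let p(1) ≤ p(2) be the ordered Day 2 p-values.

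- Plan: reject each contrast if its p ≤ 2.5%.
- Holm: reject the first if p(1) ≤ 2.5%; then reject the second if p(2) ≤ 5%.

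Anything the plan rejects, Holm rejects. The first step is the same, so the decision on HA2 itself (at least one differs) is identical. Only the second contrast can gain.

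**Step 3: power on Day 2** (simulation, 400,000 draws per row, 92 df):

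| True differences (points) | Contrast reported | Plan | Holm | Both, plan | Both, Holm |
|---|---|---|---|---|---|
| 20 and 20 | each | >99.99% | >99.99% | >99.99% | >99.99% |
| 10 and 20 | the 10-point one | 83.6% | 89.8% | 83.6% | 89.8% |
| 10 and 10 | each | 83.6%* | 87.9% | 74.0% | 82.4% |
| 8 and 8 | each | 63.1% | 68.6% | 47.6% | 58.8% |

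*Exact noncentral t; the simulated values for the two contrasts are 83.7% and 83.7%.

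Check for 10 and 10: P(at least one) = sum of the two powers − P(both). Plan: 0.8371 + 0.8366 − 0.7403 = 0.933. Holm: 0.8789 + 0.8790 − 0.8244 = 0.933. They are equal, as step 2 requires.

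**Step 4: error rates.**

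- Day 2, neither ODT differs: 4.65% under both rules (bivariate normal, correlation 0.5).
- Day 2, one ODT differs by 20 points: the error on the other contrast is 2.5% under the plan and 5.0% under Holm.
- Both days, nothing differs: 1 − 0.95 × 0.9535 = 9.4% under both rules. If all three tests were independent: 1 − 0.95 × 0.975² = 9.7%. The sum bound is 5% + 2.5% + 2.5% = 10%.
- Both days, HA1 null and one ODT truly different on Day 2: plan 1 − 0.95 × 0.975 = 7.4%; Holm 1 − 0.95 × 0.95 = 9.75%, still below 10%.

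The products in the last two items assume independence between days. The same children take part, so this is an assumption; it fits a model with a random subject effect only. The 10% bound does not need it.

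**The case against.** **The fixed rule is valid, and the gain lies off the planning point.** Both parts stand. The 2.5% rule controls Day 2 error at 4.65%, and at 20 points no power is lost. A reader might infer that the plan gives Day 2 power away; at the protocol's own inputs it does not. The gain appears only for smaller differences, and 10 points is the size planned for Day 1, not Day 2.

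**Holm doubles the error on a null contrast when the other is real.** True, from 2.5% to 5%. It is the price of the extra rejections and remains inside the 5% Day 2 bound that the 2.5% rule was set to keep.

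**Day 1 is left out of the adjustment.** A reader might infer that the 9.4% breaks a 5% promise. The documents do not support that. Section 4 separates the objectives, section 8.5.2 the hypotheses and section 8.1 the power statements, and no study-wide rate is promised. The synopsis does word the primary objective as one sentence, and section 3 says that "the most suitable formulation will be selected in 2015 for further development and registration". But nothing says that any one of the three tests decides that selection, and the Day 2 contrasts do not compare L-PZQ with Rac-PZQ. The 9.4% also requires that nothing differs anywhere.

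**Holm over all three contrasts would remove the question.** It would hold 5% across both days, but it is a trade-off. Day 1 power stays at 89.2% for true differences of 10, 20 and 20 points (Day 1, then the two Day 2 contrasts). It falls to 87.0% for 10, 10 and 10, to 82.7% for 10, 20 and 0, and to about 78% for 10, 0 and 0. That makes it the sponsor's choice, not a correction.

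**Conclusion.** The point holds as a modest improvement to a valid rule. Within Day 2, Holm keeps the 5% familywise bound and can only add rejections, whatever the true effects. The size of the benefit depends on assumptions. It is nil at 20 points. With both differences near 10 points, SD 15 and 48 completers, it is about 4 percentage points per contrast and 8 for showing both. It affects only the second contrast, not whether HA2 is declared.

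The cross-day error of about 9.4%, at most 10%, is a consequence the protocol should state. It contradicts nothing in the text.

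**What to change.** In section 8.5.2, replace the fixed 2.5% rule for the two Day 2 contrasts by Holm: test the smaller p-value at two-sided 2.5% and, only if it is significant, the other at two-sided 5%. The 2.5% in section 8.1 can stay as a conservative planning level, with a note to that effect.

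Add one sentence: the type 1 error is controlled at 5% separately for HA1 (Day 1) and HA2 (Day 2), not across both, so the chance of any false positive over the two days is about 9.4% if nothing differs and at most 10% in any case.

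The cost is wording in section 8.5.2 and the matching SAP text. It needs no extra children and no change to conduct. The one statistical price is the rise to as much as 5% on a null Day 2 contrast when the other is real. Adjustment across both days may be adopted instead if the sponsor wants a single study-wide claim and accepts the possible loss of Day 1 power.
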